## Abstract

**Background:**

Extracorporeal life support (ECLS) is used to support the cardiorespiratory function in case of severe cardiac and/or respiratory failure in critically ill patients. According to the ELSO guidelines ECLS should be considered when estimated mortality risk approximates 80%. ECLS seems an efficient therapy in terms of survival benefit, but no undisputed evidence is delivered yet. The aim of the study is to assess the health-related quality of life after ECLS treatment and its cost effectiveness.

**Methods:**

We will perform a prospective observational cohort study. All adult patients who receive ECLS in the participating centers will be included. Exclusion criteria are patients in whom the ECLS is only used to bridge a procedure (like a high risk percutaneous coronary intervention or surgery) or the absence of informed consent. Data collection includes patient characteristics and data specific for ECLS treatment. Severity of illness and mortality risk is measured as precisely as possible using measurements for the appropriate age group and organ failure. For analyses on survival patients will act as their own control as we compare the actual survival with the estimated mortality on initiation of ECLS if conservative treatment would have been continued. Survivors are asked to complete validated questionnaires on health related quality of life (EQ5D-5 L) and on medical consumption and productivity losses (iMTA/iPCQ) at 6 and 12 months. Also the health related quality of life 1 month prior to ECLS initiation will be obtained by a questionnaire, if needed provided by relatives. With an estimated overall survival of 62% 210 patients need to be recruited to make a statement on cost effectiveness for all ECLS indications.

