### Exclusion criteria

Patients in whom the ECLS in only used to bridge a procedure like a high risk percutaneous coronary intervention or during surgery.

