### Ethics

The need for ethical approval was waived by the institutional medical ethics board of the University Medical Center of Groningen (protocol number METc 2017/196), and written informed consent will be obtained from all patients or legal representatives.

The predicted mortality for every patient at the initiation of ECLS is used and compared with the actual mortality at one year of each patient. That means that every patient acts as his own control. Depending on the indication or the underlying disease, the APACHE-4, SOFA score, RESP score, or SAVE score will be used to estimate mortality. Although the used models predict hospital mortality instead of one year mortality, the vast majority of mortality is during hospital admission, so the used mortality prediction is expected to be valid for one year survival analyses as well [10, 11].

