#### Sample size calculation

Sample size calculation is based on survival with a good health related-QoL assessed with the EQ-5D-VAS questionnaire one year after initiation of ECLS treatment. Predicted mortality in usual care is 80%. Overall, expected mortality in patients with ECLS treatment is 38%. The increase in survival is thus 42%. To demonstrate an effect on survival 25 patients are needed: risk ratio 0.48 (95%CI 0.28–0.82). In usual care 90% will have a poor outcome, for sake of power analysis defined as dead or an EQ-5D-VAS below the median. With ECLS treatment this will be 69% so 132 patients are needed to demonstrate an effect on QoL. To compensate for a 5% less effect and 5% drop-outs 210 patients will be enrolled to include 200 patients with complete follow-up in the final analysis (RR 0.82; 95%CI 0.75–0.90). Based on a 38% mortality and a study duration of 3 years, 124 (62% out of 200) patients have a complete one year follow-up at the end of the study.

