## Discussion

The study uses a prospective observational design and not of a randomized controlled trial. A randomized controlled trial in ECLS would be very challenging for both the logistic and ethical reasons. We expect in the current time that the initiation of a randomized controlled trial would lead to bias and therefore impairing the external validity of the results. Our observational design with the use of predicted mortality of individual patients at the moment of initiating of ECLS as an internal comparison resembles the methods of a randomized controlled trial the most. In contrast to a randomized controlled trial our design prevents bias on the basis of indication and selection because all consecutive patients will be included. This guarantees the inclusion of a real world patient population that is clinical relevant.

ECLS is currently offered in many centers worldwide, but application per population range enormously even within countries. It is estimated that in some regions the amount of eligible patients is 10-fold the current number. Although assumed to be beneficial in terms of life saving application may be hampered by the apparent high costs and that ECLS is not covered by the health insurance in some countries. In summary, we expect that ECLS treatment is cost-effectiveness, in this case defined as having an additional benefit worth the additional cost. When cost-effectiveness is made plausible, a gradual increase in ECLS therapy is expected from which many patients will benefit.

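### The consent exclusion in the abstract is missing from the exclusion list and contradicts the claim that including all consecutive patients prevents selection bias; if early deaths go unconsented, survival can be inflated

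*Protocol article*

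**What the plan says.** Four places in the protocol article bear on who enters the cohort.

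- **Abstract, Methods.** "All adult patients who receive ECLS in the participating centers will be included". The exclusions that follow are use of ECLS purely to bridge a procedure "or the absence of informed consent".
- **Exclusion criteria.** The only entry is "Patients in whom the ECLS in only used to bridge a procedure", with examples. Consent is not mentioned.
- **Ethics.** The need for ethical approval was waived, yet "written informed consent will be obtained from all patients or legal representatives".
- **Discussion.** In contrast to a randomised trial, "our design prevents bias on the basis of indication and selection because all consecutive patients will be included".

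The Ethics section also sets out the comparison: each patient's predicted mortality at the start of ECLS against actual one-year mortality. It adds that "the vast majority of mortality is during hospital admission". The Sample size calculation section assumes 80% predicted mortality under usual care and 38% overall mortality with ECLS.

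**The concern.** The sections cannot all hold. If absence of consent excludes a patient, the cohort is the consented subset and the Discussion's reason for ruling out selection bias falls away. If everyone is included, the abstract is wrong.

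The contradiction matters because lack of consent is plausibly tied to outcome. According to the Background, ECLS is used for acute cardiac or respiratory failure and to support resuscitation, and extracorporeal resuscitation is one of the six subgroups. Such patients can rarely consent beforehand. Most deaths are expected in hospital, the period in which consent would be sought. A patient who dies before anyone can be asked has no consent and, under the abstract's rule, leaves the cohort.

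There is no control group, so the contrast between observed and predicted mortality carries the survival result, the QALY gain and the cost-effectiveness ratio. Losing early deaths raises observed survival. It also removes patients who incurred hospital costs with almost no QALYs, which would tend to flatter the cost per QALY.

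**Working it through.** **The plan's own figures.** 80% − 38% = a 42-point survival gain; 62% × 200 = 124 one-year survivors; 200 × 1.05 = 210 enrolled. All reproduce. The figures are not the problem.

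**What the documents do not give.** The number of patients who die without consent, the number of survivors without consent, and the predicted mortality of either group. These are assumptions below, shown as ranges.

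**Calculation A: 210 consented patients with 38% mortality (79.8 deaths), plus k lost deaths.**

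- True mortality = (79.8 + k) / (210 + k).
- With mean predicted mortality of 80% among all treated patients and p among the lost patients, the comparator among the consented = (0.80 × (210 + k) − p × k) / 210.
- Net bias = (true mortality − 38%) − (80% − comparator among the consented).

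If p = 80% the comparator does not move. If p = 100%, the upper limit, it falls as far as it can under these assumptions.

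| k | True mortality | True gain (points) | Net bias, p = 80% | Comparator, p = 100% | Net bias, p = 100% |
|---|---|---|---|---|---|
| 10 | 89.8/220 = 40.8% | 39.2 | 2.8 | 166/210 = 79.0% | 1.9 |
| 20 | 99.8/230 = 43.4% | 36.6 | 5.4 | 164/210 = 78.1% | 3.5 |
| 30 | 109.8/240 = 45.75% | 34.25 | 7.75 | 162/210 = 77.1% | 4.9 |

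These values of k mean that 10/89.8 = 11%, 20/99.8 = 20% and 30/109.8 = 27% of all deaths are lost.

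**Calculation B: 38% is the mortality of all treated patients, and a share f of deaths is lost.** The Sample size calculation section gives 38% as an overall figure, so this reading is closer to the text.

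- Observed survival = 0.62 / (1 − 0.38f).
- f = 10%: 0.62/0.962 = 64.4%. f = 20%: 0.62/0.924 = 67.1%. f = 30%: 0.62/0.886 = 70.0%.
- Overstatement: 2.4, 5.1 and 8.0 points before any offset.
- At f = 20% and p = 100%, the comparator falls to (0.80 − 0.076)/0.924 = 78.4%, leaving about 3.5 points.

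The two calculations agree on the order of magnitude.

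**When survivors also lack consent.** With a share g of survivors missing, observed survival = 0.62(1 − g) / [0.62(1 − g) + 0.38(1 − f)].

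- f = 20%, g = 20%: 62.0%, no bias.
- f = 20%, g = 10%: 0.558/0.862 = 64.7%.
- f = 20%, g = 30%: 0.434/0.738 = 58.8%, a bias against ECLS.

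The direction therefore depends on non-consent being more frequent among those who die.

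**The case against.** The other side has several sound points.

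- **Representatives may consent.** The Ethics section allows this, and the Outcome measures section has relatives helping with the pre-ECLS questionnaire at admission, so early family contact is planned. Incapacity or early death does not by itself mean exclusion. This stands and makes the loss smaller. It does not remove it, since a representative must also be reached in time.
- **The comparator moves too.** It is each included patient's own prediction. If the lost patients were sicker, their high predictions leave as well. This stands, but even at 100% predicted mortality the offset in the working is partial.
- **The primary outcome is largely untouched.** EQ-5D-5L at 12 months is completed by survivors, and survival is secondary. This stands. Survival, QALYs, costs and the death-or-low-VAS outcome used for the sample size are still exposed.
- **The direction of the survival result is safe.** Even at 30 lost deaths a gain of about 34 points remains. This stands for survival; the cost-effectiveness ratio has no such evident margin.
- **Consent timing and screening logs belong in the full protocol.** Their absence from an article is fairly not held against it. The contradiction between the sections is on the page and remains.

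A reader might go further and infer that survival is overstated as a matter of fact, or that the 38% measures how many patients will be lost. The documents support neither. They do not say how many patients die without consent, and 38% is overall expected mortality, which only bounds the loss. A reader might also take the ethics waiver as permission to use unconsented records. It waives ethical approval, and the same sentence requires written consent.

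**Conclusion.** The point holds as an internal contradiction with a plausible but unquantified bias. The abstract excludes patients without consent, the exclusion list does not, and the Discussion relies on a completeness that the abstract denies. The claim that selection bias is prevented is therefore unsupported as written.

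If early deaths go unconsented more often than survivors do, observed survival and QALYs are inflated and early hospital costs are lost. For an assumed 10, 20 or 30 lost deaths beyond 210 consented patients, net bias in the survival contrast is roughly 2–3, 3.5–5.5 or 5–8 points. This rests on 38% mortality among the consented, a mean prediction of 80% among all treated patients, predictions of 80–100% for the lost patients, and no survivors lost. The bias is zero if no deaths are lost or if non-consent is unrelated to survival. This is a risk to be measured, not an overstatement already shown.

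**What to change.** 1. Reconcile the abstract, Exclusion criteria, Ethics and Discussion so that they state one rule on consent and entry to the cohort.
2. Remove or qualify the Discussion's statement that the design prevents selection bias.
3. Keep a log of all ECLS-treated patients at each centre. Report the number and hospital mortality of those without consent, in anonymised or aggregate form.
4. Add a sensitivity analysis of survival and cost-effectiveness that includes these patients.
5. Include all treated patients in the main survival and hospital-cost analyses, with consent needed only for the questionnaires, only if the ethics board confirms that this is allowed.

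The cost is a screening log, one additional analysis and, for step 5, a query to the ethics board. No extra patient visits are needed. The log should be in place before recruitment starts, because deaths that were never logged may be hard to recover later.

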**Discussion:**

If our hypothesis that ECLS treatment is cost-effective is confirmed by this prospective study this could lead to an even broader use of ECLS treatment.

**Trial registration:**

The trial is registered at (NCT02837419) registration date July 19, 2016 and with the Dutch trial register, http://www.trialregister.nl/trialreg/admin/rctview.asp?TC=6599

## Background

Extracorporeal life support (ECLS) by means of extracorporeal membrane oxygenation (ECMO) utilization can support the heart and lung for an extended period of time, up to months, an is deployed in the Intensive Care Unit (ICU). The indication for ECLS is acute, potentially reversible cardiac or respiratory failure, when conventional therapy has been inadequate [1]. In addition, ECLS can also be used in patients with terminal respiratory or cardiac failure as a bridge to transplant, and to support cardiopulmonary resuscitation; extracorporeal cardiopulmonary resuscitation.

ECMO is proven beneficial in mature infants with severe but potentially reversible respiratory failure leading to a significantly improved survival without increased risk of severe disability [2]. The increased use of ECLS after the CESAR trial, during the H1N1 pandemic and advances in device technology renewed interest in ECLS utilization in adults [3]. ECLS seems an efficient therapy for cardiac and respiratory failure, but unfortunately no undisputed evidence from randomized controlled trials is delivered yet. Furthermore, currently no detailed information on costs of ECLS therapy is available. The urge for economic evaluations emerges from the increasing deployment of ECLS. The CESAR trial was the first adult trial performed for cost comparison between ECLS and mechanical ventilation for severe adult respiratory distress syndrome (ARDS) [3]. This trial provided data concerning the subgroup of patients with severe ARDS suitable for veno-venous ECLS and compared referral to a center that offered ECLS with conventional management at the original center, not ECLS therapy itself; 68 out of 90 referred patients actually received ECLS therapy. Mean health-care costs per patient were more than twice as high for patients allocated to consideration for ECLS than for those allocated to conventional management. We previously performed a detailed exploratory cost study to gain insight in the hospital costs related to ECLS therapy regardless of indication and found that an ECLS patient carried a mean total hospital cost of €109.407. With a total of 72 patients, our study is the largest economic evaluation, providing a detailed insight of hospital costs in adults treated with ECLS and thus constitutes a first step in assessing it’s cost-effectiveness [4]. The next step in assessing the cost-effectiveness of ECLS therapy is to proceed with an economic evaluation in which costs from a societal perspective are considered. More knowledge about outcome variables such as life years gained and quality adjusted life years (QALY’s) needs to be gathered in a prospective manner. Then, interpretation of the total hospital costs in context to the outcome of ECLS patients is possible with the aim to study whether patients actually benefit from ECLS treatment and at what costs.

A direct comparison between usual care and ECLS, e.g. by means of a randomized trial, is very complex since standard treatment (no ECLS) will result in death in a vast majority of cases. However, several ICU scoring systems exist that predict hospital mortality of individual patients. Depending on the indication, i.e. underlying disease, RESP score, SAVE-score, APACHE-4, SAPS-III or SOFA score are the most reliable for that purpose [5–9].

## Methods/design

The design is a multi-center prospective observational cohort study with the aim to assess the health-related quality of life after ECLS treatment and the associated costs. We expect that survivors of ECLS therapy have a good quality of life and life expectancy. Lifetime predicted costs for QALYs are expected to be cost-effective. Therefore our hypothesis is that ECLS treatment is cost effective.

### Inclusion criteria

All adult patients who receive ECLS will be included. With our consortium we cover nearly all ECLS treatments in The Netherlands. In general, according to the ELSO guidelines, ECLS can be considered in acute severe heart and/or lung failure with high mortality risk despite optimal conventional therapy. ECLS is indicated in most circumstances at 80% mortality risk. Severity of illness and mortality risk is measured as precisely as possible using measurements for the appropriate age group and organ failure.

### Exclusion criteria

Patients in whom the ECLS in only used to bridge a procedure like a high risk percutaneous coronary intervention or during surgery.

### Ethics

The need for ethical approval was waived by the institutional medical ethics board of the University Medical Center of Groningen (protocol number METc 2017/196), and written informed consent will be obtained from all patients or legal representatives.

The predicted mortality for every patient at the initiation of ECLS is used and compared with the actual mortality at one year of each patient. That means that every patient acts as his own control. Depending on the indication or the underlying disease, the APACHE-4, SOFA score, RESP score, or SAVE score will be used to estimate mortality. Although the used models predict hospital mortality instead of one year mortality, the vast majority of mortality is during hospital admission, so the used mortality prediction is expected to be valid for one year survival analyses as well [10, 11].

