#### Statistics

With the additional information on costs (apart from direct hospital costs already available) assessed within this study it is now possible to calculate the costs of ECLS therapy related to mortality. Based on case-fatality and health related-QoL we will be able to assess QALY’s. For this calculation the predicted mortality at initiation of ECLS therapy is used for comparison. Many patients treated with ECLS survive only after lung transplantation, heart transplantation or implantation of a left ventricular assist device. Life expectancy of the study population can thus be based on the average expectations of that particular patient category. The remaining patients who were treated with ECLS as a bridge to recovery have a reasonable good quality of life [10, 12]. Based on our follow-up study of ICU patients we expect that the median health related-QoL in surviving patients will be 0.83 after one year, which results in 0.36 QALY gained per treated patient. Although additional total healthcare costs and loss of income will be substantial and assumed to exceed €172,200 after one year compared with usual care, lifetime-predicted costs and QALYs is expected to be cost-effective due to the relatively good life-expectancy of survivors. With data from 200 patients of which 62% survive until one-year follow-up we will be able to make a statement about cost-effectiveness for all indications for ECLS.

A cost effectiveness analysis as well as a Budget Impact Analysis will be performed in accordance with the Dutch guidelines [13, 14].

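### Observed one-year mortality is compared with predicted hospital mortality, which modestly understates the one-year survival and QALY gain of ECLS

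*Protocol article*

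**What the plan says.** The study has no control group. The Abstract (Methods) defines the comparison: "we compare the actual survival with the estimated mortality on initiation of ECLS if conservative treatment would have been continued". The Ethics section states how it is done. Predicted mortality at the start of ECLS "is used and compared with the actual mortality at one year of each patient". Depending on indication or underlying disease, "the APACHE-4, SOFA score, RESP score, or SAVE score will be used to estimate mortality".

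The same paragraph acknowledges that the two sides have different horizons. It says "Although the used models predict hospital mortality instead of one year mortality, the vast majority of mortality is during hospital admission" and concludes, with two references, "so the used mortality prediction is expected to be valid for one year survival analyses as well".

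The Statistics section carries the prediction into the QALY calculation: "For this calculation the predicted mortality at initiation of ECLS therapy is used for comparison". The cost-effectiveness section sets a one-year horizon for the trial-based analysis and then extrapolates its results to a lifetime with a decision model.

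**The concern.** The two sides of the comparison are measured over different periods. On the ECLS side, every death up to one year counts, including deaths after discharge. On the usual-care side, the prediction stops at hospital discharge, and whoever is predicted to leave hospital alive is counted as alive at one year.

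This error has a known direction. Mortality accumulates, so one-year mortality without ECLS is at least as high as hospital mortality without ECLS. Using the lower figure as the one-year control makes the gain from ECLS look smaller than it is. What is at stake is the one-year survival comparison, the QALY gain, the cost per QALY built on it, and the lifetime model that starts from these results.

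**Working it through.** **Inputs**
- Usual-care mortality 80%, ECLS mortality 38%, gain in survival 42 points (Sample size calculation).
- Expected utility of survivors 0.83, QALY gain 0.36 per treated patient, and additional cost of €172,200 after one year (Statistics).
- Share *h* of predicted usual-care hospital survivors who die between discharge and one year: not given, so it is varied.

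**Step 1: the plan's own figures.** Gain = 0.80 − 0.38 = 0.42, as stated. QALY gain = 0.42 × 0.83 = 0.349. The plan states 0.36, about 3% higher. The recomputed 0.349 is the reference below.

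**Step 2: put the control on the one-year horizon.** Read the 80% as hospital mortality, which is what the scores are said to predict. The predicted hospital survivors are then 20%, and one-year usual-care mortality is 0.80 + 0.20*h*. The one-year gain is 0.42 + 0.20*h*, and the understatement is 0.20*h*.

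| *h* (assumed) | One-year usual-care mortality | One-year gain | QALY gain (× 0.83) | Understatement |
|---|---|---|---|---|
| 0% | 80% | 42 points | 0.349 | none |
| 5% | 81% | 43 points | 0.357 | 1 point, 0.008 QALY |
| 10% | 82% | 44 points | 0.365 | 2 points, 0.017 QALY |
| 20% | 84% | 46 points | 0.382 | 4 points, 0.033 QALY |
| 50% | 90% | 52 points | 0.432 | 10 points, 0.083 QALY |

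The logical limit is *h* = 100%, an understatement of 20 points. The QALY column follows the plan in multiplying survival at one year by 0.83. It therefore charges a full year's utility for each later death. Deaths spread over the year would cost less, so the QALY differences are upper values for each *h*.

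**Step 3: a cross-check from the ECLS side.** Suppose 80% to 95% of the planned 38% one-year mortality occurs in hospital (an assumption in the spirit of the plan's reasoning).
- At 95%: hospital mortality 0.38 × 0.95 = 36.1%; later deaths 1.9% among 63.9% discharged alive, or 3.0%.
- At 80%: hospital mortality 0.38 × 0.80 = 30.4%; later deaths 7.6% among 69.6% discharged alive, or 10.9%.

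Applying these rates to the 20% predicted usual-care survivors gives 0.20 × 3.0% = 0.6 points and 0.20 × 10.9% = 2.2 points.

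**Step 4: effect on one-year cost per QALY, cost held fixed.** €172,200 / 0.3486 ≈ €494,000 as planned. At *h* = 5% it is €172,200 / 0.3569 ≈ €482,000, and at *h* = 20% it is €172,200 / 0.3818 ≈ €451,000.

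**The case against.** The strongest reply is that the article discloses the mismatch, gives a reason and cites two sources, so this is an acknowledged assumption and not an oversight. The bias also runs against the study's own hypothesis, and it concerns secondary results. The primary outcome is EQ-5D-5L at 12 months and the primary economic aim is to estimate societal costs; neither needs a predicted mortality. The sample size uses a fixed 80%. Scenario analyses are already planned, and their detail may stand in an analysis plan that is not shown.

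Most of this stands and limits the weight of the point. It does not remove it. If most deaths do occur in hospital, the error is small, but it is not zero and always has the same sign. The article also fixes the mismatched comparison as the method, so this is not merely detail left for later.

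Two stronger readings are tempting.

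- A reader might infer that RESP and SAVE predict outcome in patients already on ECLS. For patients scored that way, the control would then not be usual care and the gain could shrink towards zero. The documents do not support this. The Background says only that "several ICU scoring systems exist that predict hospital mortality of individual patients" and lists these two among them. The acronyms are not expanded, and nothing says whether the predictions apply with or without ECLS. It is no part of this point.
- A reader might set a hospital-survival gain of 44 to 50 points (80% minus 36.1% or 30.4%) against the 42 points and call the difference the error. Those are two different quantities. The error in the one-year gain is only the post-discharge mortality missing from the usual-care side.

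**Conclusion.** The point holds as a modest, conservative bias. Observed one-year deaths are set against predicted hospital deaths, and the same prediction feeds the QALY comparison, so the one-year gain is understated. With the planned 80% and 38%, the understatement is 1 to 4 points (about 0.01 to 0.03 QALY) if 5% to 20% of predicted usual-care hospital survivors die by one year. It is 0.6 to 2.2 points if their post-discharge mortality equals that implied for ECLS patients in the cross-check.

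These sizes rest on assumed post-discharge mortality and on the scores being right about hospital mortality without ECLS. The direction needs only the second assumption. The mismatch makes the gain look smaller than it is and cannot explain a positive one. The sample size and the primary outcome are unaffected. The change is worth making because it is easy and gives a better comparison, but the study does not stand or fall by it.

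**What to change.** 1. Make the main survival comparison like for like: observed hospital mortality against predicted hospital mortality, reported as an observed/expected ratio with a confidence interval.
2. For the one-year survival and QALY comparison, apply a post-discharge mortality to the predicted usual-care hospital survivors too. State its source and show results over a range such as 5% to 20%.
3. Within the scenario analyses already planned, vary the counterfactual mortality over a stated range, for example 60% to 90%. At 38% ECLS mortality this spans gains of 22 to 52 points (0.60 − 0.38 and 0.90 − 0.38), so it also shows how far the conclusion depends on the prediction itself.

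Cost: revised analysis wording and a few extra analyses, with no new patients or study procedures. The drawback is that the one-year analysis then depends openly on an assumed post-discharge rate. The present method also assumes one, namely zero.
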